Individuals may be included who: report smoking at least 10 cigarettes/day for the previous six months, produce a breath sample with a CO level > 9 ppm, report being motivated to quit, and are able to read and write English. Medical screening at baseline will ensure that participants can safely be prescribed any of the included medications (e.g., no uncontrolled hypertension, history of bipolar illness, recent myocardial infarction, current alcohol dependence with risk of seizure, seizure history, history of bulimia or anorexia nervosa, or current use of a MAO inhibitor). In addition, any individual who reports regular thoughts of suicide or self-harm will be assessed by a clinical psychologist, and those judged to be at risk for suicide will be excluded and offered referrals to appropriate treatment resources.

Figure 1: Treatments for the 1,520 study participants randomized to Project 1: Efficacy For the purposes of this grant application, participants will be considered part of Project 1: Efficacy from the time of their enrollment and completion of pre-quit assessments until their one-year post-quit anniversary date. They will be considered part of the current project (Project 2: Longterm Outcomes) from their one-year post-quit anniversary date until at least three years after the quit attempt anniversary date. Enrollment for Project 1 will take place over the first two years of this five-year TTURC grant. Enrollment in Project 1 will commence about six months after the start of grant funding and will continue for approximately 18 months.

*Enrollment*. Enrollment for Project 2 (Longterm Outcomes) will begin at around 18 months (when the first participant in Project 1 reaches his/her 12 month quit date anniversary) and continues through month 36 (when the last participant in Project 1 reaches his/her 12 month quit date anniversary). The end of Project 1 and the start of Project 2 are designed to be seamless for participants. Based upon cost considerations and power, we will invite only 900 Subjects from Project 1 to participate in Project 2.

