**Expected Abstinence Rates and Attrition**

Based on projections detailed in Project 1, we expect the overall biochemically-confirmed one-week point–prevalence abstinence rates to be 27.6% at six months and 23.6% at 12 months. A survey of some dozen clinical trials (e.g., 151,154,205-207) shows that a typical decline in abstinence rates from 6 to 12 months is about 4%. A similar adjustment was applied to our expected six-month abstinence rates to yield projected 12-month abstinence rates (See Table 2). Comparisons with actual reported 12 month rates 151,153,207-211 shows precedence for these estimates.

*Attrition*. Attrition in Project 2 will be influenced by attrition that occurs during Project 1 (the first year after the quit attempt; see Project 1 for more details). Our attrition expectation for Project 1 suggests one-year attrition rates of 10-20%, based on prior research. For instance, in our most recent clinical trial,13810% of the samplestopped study participation over the 12-month follow-up period. This study is highly relevant to the current attrition estimate since it involved similar assessment and ethnic representation as is proposed for Project 1. That study, however, did not include additional aggressive steps that we will follow to minimize attrition in the current research (see “Steps to reduce attrition” below). In two of our other recent clinical trials having extensive assessment burdens and visit schedules, attrition was about 18% at one year. The attrition projection of 15% over the course of Project 1 therefore, seems reasonable given the retention steps to be employed in the proposed study. Thus, we envision that 15% of 1,520 participants enrolled Project 1 will attrit by month 12, leaving approximately 1,292 available for enrollment in Project 2 (many more than the target enrollment for Project 2 of 900).

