*Smoking outcomes.* Smoking status will be somewhat fluid over the two years of follow-up for subjects in Project 2 as some participants will transition between smoking and abstinence during this time. Research suggests that between 3 – 5% of abstainers at the end of Year one (end of Project 1) will resume smoking each year over the course of follow-up Years 2 & 3 of Project 2.13 Based upon this, we estimate an annual relapse rate of 4% among those confirmed to be successful quitters one year post-quit (See Table 3).

Conversely, data suggest that a significant percentage of those relapsing by Year 1 or later will re-establish abstinence. The large COMMIT longitudinal study suggests a natural quit rate of about 4%/year over several years223. These figures agree with those from the Working Well Trial, the Normative Aging Study, and others showing approximate long term 3% to 5% spontaneous quit rate/year.12,101,224 Some studies such as the Health and Retirement Study113 report higher spontaneous quit rates but the older age range of those participants makes the data less relevant. It is possible that quit rates over Follow-up Years 2 & 3 will be somewhat higher than 4% in this study due to follow-up contacts and the fact that participants entered the study because of an interest in quitting smoking. However, we will use a 4% quit rate as a conservative estimate for both Follow-up Years 2 & 3 (Table 3). We recognize that newly abstinent subjects cannot be treated as continuously abstinent. However, our data will permit continuous measures of smoking over the three-year follow-up period.

Some analyses will use subjects who have been continuously abstinent for the entire 3-year follow-up. Given the abstinence and attrition estimates in Table 3, we expect 300 subjects to fulfill criteria for continuous abstinence at the end of Year 3.

Table 4. Assessment schedules (Orientation visits part of Project 1)

| **Evaluation** | Orientation  (3 Visits) | One Year In-Person Visit | 18-month Phone Follow-Up | Two Year In-Person Visit | 30-month Phone Follow-Up | Three Year In-Person Visit |
| --- | --- | --- | --- | --- | --- | --- |
|
|
| Sign Informed Consent and HIPAA | X |  |  |  |  |  |
| Demographics | X |  |  |  |  |  |
| Smoking History | X |  |  |  |  |  |
| Wisconsin Inventory of Smoking Dependence Motives (WISDM-68) | X | X |  | X |  | X |
| Wisconsin Predicting Relapse in Smoking Measure (WI-PRISM) | X |  |  |  |  |  |

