Figure 5 depicts an example of a multivariate unconditional latent trajectory model (LTM) for exploring alcohol use and smoking (modeled with only 4 repeated measures). Such models might also be used to explore relations between smoking and psychiatric symptoms, and between smoking and weight gain. Control variables such as those described in the “Predicting Discrete Endpoints” will be used as exogenous variables (MPQ Constraint, Gender, and Smoking in the Social Network). One exemplar set of predictions (Figure 5) would be that Gender will influence both initial drinking and smoking indices (Intercepts) with males showing higher levels. Low levels of trait Constraint would predict high initial smoking and drinking, and predict high levels of smoking over time. Post-quit smoking in the Social Network would also predict a reduced decline in smoking over time. Smoking and drinking might be inter-related in that higher smoking intercepts predict reduced declines in drinking over time.

Power

After accounting for relapse and attrition (initial N=900), we expect that data for at least 300 continuously abstinent and 450 smoking participants to be available for analysis. These estimates are based on the expectation that approximately 9% of the participants enrolled in Project 2 will either relapse (approximately 4% per year) or drop out of the study (approximately 5% per year) in years 2 and 3. The large number of primary and secondary hypotheses precludes presentation of power estimates for all possible comparisons. Two power analyses are presented below of central, discrete endpoint hypotheses.

*Long-term smoking status and atherosclerotic progression:* The best relevant estimates of CIMT effect sizes were reported by Howard et al.1 These authors analyzed CIMT change over a 3-year period in terms of smoking status (current, past, never) and ETS exposure. Howard et al.1 used mean common CIMT as the measure of progression (CIMTmean ). The authors computed linear regression models that controlled for demographic, life-style, and other risk factors and found a significant difference between current and past smokers of 7.3 m, equivalent to a 20% difference in progression.

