**E. HUMAN SUBJECTS**

Risks to the Subjects

*Human Subjects Involvement and Characteristics:* While 1520 participants will be enrolled at the baseline of this study (Project 1: Efficacy), only 900 will participate in the proposed follow-up study (Project 2). All individuals who report 7-day point-prevalence abstinence at Week 52 of Project 1 (approximate n = 360) will be invited to participate in the proposed study. The remainder of Project 2 participants (approximate n = 540) will be randomly selected from all relapsed participants from Project 1. All participants will be 18 years of age or older. Inclusion criteria at baseline for Project 1 will be: (1) smoking at least 10 cigarettes/day (on average) for the previous 6 months, (2) a breath sample with a CO level > 9 ppm, (3) being motivated to quit, (4) able to read and write English, (5) agree to respond to EMA prompts throughout the day, (6) plan to remain in the treatment catchment area for at least 12 months after the initiation of treatment, (7) no medical contraindications for use of bupropion (e.g., no uncontrolled hypertension, history of bipolar illness, recent myocardial infarction, recent heavy alcohol use, seizure history, or use of MAO inhibitors or other contraindicated medications), (8) no imminent risk of suicide, (9) no other member of the household is participating, and (10) women are not pregnant and agree to prevent pregnancy during the course of study pharmacotherapy. There will be no restrictions on participation based on sex or race.

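### The 300 participants called continuously abstinent for three years are counted from 7-day abstainers at month 12, so 300 is an upper bound and the CIMT power of .81 is overstated for that definition

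*Protocol*

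**What the plan says.** The protocol uses two definitions of abstinence for one group.

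- **Entry to the group.** Under Expected Abstinence Rates and Attrition: "we expect the overall biochemically-confirmed one-week point–prevalence abstinence rates to be 27.6% at six months and 23.6% at 12 months". Under E. Human Subjects: "All individuals who report 7-day point-prevalence abstinence at Week 52 of Project 1 (approximate n = 360) will be invited to participate". The Recruitment and Enrollment section gives the same estimate of 360 abstinent people, plus about 540 relapsers.
- **Name of the group at the end.** Under Smoking outcomes: "Some analyses will use subjects who have been continuously abstinent for the entire 3-year follow-up". The next sentence gives the expected number: "we expect 300 subjects to fulfill criteria for continuous abstinence at the end of Year 3".
- **Use in power.** The Power section opens with "we expect that data for at least 300 continuously abstinent and 450 smoking participants to be available for analysis". It explains these numbers by about 4% relapse and 5% dropout per year in years 2 and 3. The CIMT paragraph concludes with a power of .81 and names the contrast as smokers against continuously abstinent ex-smokers. The psychiatric paragraphs use the same group sizes but call the group only abstinent. They state power above .80 for 30% v 20% and .79 for 30% v 21%.

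**The concern.** Someone who smoked for most of year 1 and stopped eight days before the month-12 call meets the entry rule. That person does not meet a three-year continuous definition. The protocol accepts this principle elsewhere. Smoking outcomes says that people who become abstinent later cannot be counted as continuously abstinent, but applies this only to quitters in years 2 and 3. The telephone-visit and construct sections list continuous and point-prevalence abstinence as separate measures.

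More than a label is at stake. CIMT is measured before the quit day and at year 3, and psychiatric incidence is counted over the three years after the quit day. Year-1 smoking falls inside both windows. Either fewer than 300 people meet the stated definition, or the 300 include people with year-1 exposure and the assumed contrast may be diluted.

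**Working it through.** **Inputs, all from the protocol.** 1,520 randomised in Project 1; 23.6% one-week point-prevalence abstinence at 12 months; 360 abstinent and 540 relapsed enrolled; 4% relapse and 5% attrition per year in years 2 and 3. CIMT: change 5.28, SD 5.0, 20% difference, alpha .05. Psychiatric incidence: 30% in smokers against 20% or 21%. Sidedness is not stated; two-sided tests without continuity correction reproduce the protocol's figures.

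**1. Group sizes.**
- Abstinent at month 12: 1,520 × 0.236 = 358.7, about 360.
- After years 2 and 3: 360 × (1 − 0.09)² = 298.1, or 360 × (0.96 × 0.95)² = 299.4 if the two losses are compounded separately.
- Smokers: 540 × 0.91² = 447.2, about 450.

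The 300 and 450 reproduce, with no term for smoking in year 1.

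**2. CIMT power at 300 v 450.** Difference = 0.20 × 5.28 = 1.056. Standard error = 5.0 × √(1/300 + 1/450) = 0.3727. Power = Φ(1.056/0.3727 − 1.96) = Φ(0.874) = .809, against .81 stated.

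**3. Psychiatric power at 300 v 450.** Power = Φ[(difference − 1.96 × SE₀)/SE₁], where SE₀ uses the pooled rate and SE₁ the separate rates.
- 30% v 20%: pooled rate 0.26, SE₀ = 0.0327, SE₁ = 0.0316; power .872, against the stated claim of more than .80.
- 30% v 21%: pooled rate 0.264, SE₀ = 0.0329, SE₁ = 0.0319; power .789, against .79 stated.

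**4. Effect of the definition.** Let f be the share of the 300 who did not smoke at any time in year 1. The three-year continuous group is then 300 × f, and it equals 300 only if f = 1. The protocol gives no value for f, so the values below are assumptions. Smokers are held at 450.

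| f | n abstinent | CIMT | 30% v 20% | 30% v 21% |
|---|---|---|---|---|
| 1.0 | 300 | .81 | .87 | .79 |
| 0.9 | 270 | .78 | .85 | .76 |
| 0.8 | 240 | .75 | .82 | .73 |
| 0.5 | 150 | .61 | .67 | .57 |

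**5. Abstainers needed for power .80 against 450 smokers.**
- CIMT: 289. The loss from 300 is 11/300, about 4%.
- 30% v 20%: 223. The loss from 300 is 77/300, about 26%.
- 30% v 21%: 314, so this comparison is already just under .80 at 300.

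**The case against.** The arithmetic is correct, and every stated figure reproduces. The fault is a mismatch of definitions. Several further points on the other side have weight.

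- **The three-year group is not the only basis for inference.** The protocol limits it to some analyses, allows abstinence to be coded continuously, and prefers percent days smoking with heaviness measures for modelling over time. It calls the enrolment figures inexact and expects covariates to reduce error. This lowers the consequence but does not repair the count, because the published power rests on the dichotomous 300 v 450.
- **The psychiatric text says only abstinent.** If that comparison uses people abstinent at month 12 and thereafter, its stated power stands. The Power section does introduce the 300 as continuously abstinent before both analyses, so the text leaves this open.
- **Table 3 and the criteria for continuous abstinence cannot be inspected.** Table 3 is not in the text at hand and the criteria are not spelled out. They might tolerate year-1 lapses. The stated inputs give 300 without the table, however, and the wording still covers the whole three years.
- **The three years might mean months 12 to 36.** This does not stand. The same section describes Project 2 as two years of follow-up, so a three-year window includes year 1.
- **Excluded abstainers could join the comparison group.** With the total kept at 750, CIMT power is .77 at 240 abstainers and .64 at 150, still below .81.

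A reader might go further and infer that both power analyses fail, that a particular smaller N should replace 300, or that recent re-quitters relapse faster than 4% a year. The protocol supports none of these. The 30% v 20% claim survives a loss of up to about 26%. No continuous-abstinence rate is given from which to compute another N. The 4% relapse rate is applied to all month-12 abstainers without distinction.

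**Conclusion.** The mismatch is real and should be corrected, though it does not undermine the design. On the protocol's inputs, 300 is an upper bound on three-year continuous abstinence, where the text presents it as an expected and even a minimum number. The direction is certain; the size is not.

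- **CIMT .81** is overstated for the contrast it names and has almost no reserve.
- **.79 for 30% v 21%** also falls with any loss, provided the psychiatric comparison uses the three-year continuous group.
- **More than .80 for 30% v 20%** is not shown to be wrong. It would fail only below about 223 abstainers.

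These results assume 450 smokers, two-sided alpha .05 and the protocol's own effect sizes. The table is a sensitivity range over an unknown share and does not estimate that share.

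**What to change.** Choose one of two routes.

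1. **Match the definition to the count.** Define the abstinent group for these comparisons as 7-day abstinent at month 12 and continuously abstinent from month 12 to month 36. Remove the three-year wording from the 300 and from the power statements. State that year-1 smoking lies inside both outcome windows and may dilute the contrast. Report the group abstinent since the quit day as a sensitivity analysis with its own N. The stated group sizes and powers can then stay, subject to that dilution.
2. **Match the count to the definition.** Keep three-year continuous abstinence, state an expected continuous-abstinence rate with its basis, derive N from it, and restate both power analyses as a function of that rate.

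Either way, say which abstinent group the psychiatric comparison uses.

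The cost is wording and, on the second route, a restated power table. No new data are needed, because the abstinence calendar is already reviewed at each contact. The downside is a less pure abstinent group on the first route, or less favourable stated power on the second.

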| Fagerström Test of Nicotine Dependence (FTND) | X |  |  |  |  |  |
| Wisconsin Smoking Withdrawal Scale (WSWS) | X | X | X | X | X | X |
| Multidimensional Personality Questionnaire-Short Form (MPQ-S) | X |  |  |  |  |  |
| Positive and Negative Affect Scale (PANAS) | X | X | X | X | X | X |
| Depression Proneness Inventory (DPI) | X |  |  |  |  |  |
| Holmes-Rahe Social Readjustment Rating Scale | X | X |  | X |  | X |
| International Physical Activity Questionnaire (IPAQ) | X | X |  |  |  | X |
| PrimeScreen (dietary questionnaire) | X | X | X | X | X | X |
| Food Frequency Questionnaire (FFQ) | X | X |  | X |  | X |
| Vital Signsa | X | X | X | X | X | X |
| Suicidality Assessment | X | X |  | X |  | X |
| Complete Physical Exam | X |  |  |  |  |  |
| Waist Circumference | X | X |  | X |  | X |
| National Comorbidity Survey – Revised (NCS-R-CIDI)b | X | X |  | X |  | X |
| Short Inventory of Problems (SIP-2R) – Alcohol related problems | X | X | X | X | X | X |
| Social Network Interview | X | X |  | X |  | X |
| Kansas Marital Satisfaction Scale c | X | X |  | X |  |  |
| Quality of Life Inventory (QOLI) | X | X |  | X |  | X |
| Pregnancy Test for women | X |  |  |  |  |  |
| Ultrasound Carotid Intima–Media Thickness (CIMT) | X |  |  |  |  | X |
| Ultrasound Brachial Artery Response Test (UBART) | X |  |  |  |  |  |
| Exercise Stress Test | X |  |  |  |  | X |
| Pedometer Training and Assessment | X | X |  | X |  | X |
| Blood Drawd | X | X |  |  |  | X |
| Smoking Statuse | X | X | X | X | X | X |
| **Time Required For Each Visit (in hours)** | **8** | **4** |  | **2** |  | **4** |

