**Measurement and Data Collection Plan**

For Project 1, baseline questionnaire/interview data as well as physiological assessments will be collected during visits occurring prior to the quit day. This pre-quit data will also provide baseline data for Project 2. In addition to this baseline data, many of these same assessments will be collected at 12, 24, and 36 month (in-person) and 18, 30, and 42 month (telephone) follow-up contacts for Project 2. The timetable for data collected over the three years that comprise Projects 1 and 2 is depicted in Table 4.

*Annual In-Person Clinic Visits (Months 12, 24, and 36).* Participants enrolled in Project 2: Longterm Outcomes will attend an in-person clinic visit at one, two, and three years (12, 24, and 36 months) post-quit attempt. During these visits, participants will repeat many of the baseline assessments (see Table 4) including information to determine continuous and point-prevalence abstinence, the nature of any relapse event (environmental and social context, stressors, alcohol use, and so on), use of any new cessation aids, new quit attempts, and withdrawal and affective status (WSWS, PANAS, etc.). Suicidality will be assessed and appropriate referrals made in the event that suicide risk is determined.

Table 4 also lists other assessments that will take place at each annual in-person visit. Virtually all of the baseline paper-pencil questionnaires will be re-administered as well as the NCS-R-CIDI. In addition, some physiologic measures will be assessed including weight, body mass index, vital signs, waist circumference, and carbon monoxide (provided via a breath sample). Selected physical measures will be collected at some of these visits. For instance, the Carotid IMT, Exercise Stress Test, and NMR LipoProfile tests will be performed at the Baseline and Year 3 Visit. Brachial artery endothelial function will be tested at the Baseline and Year 1. Blood tests will completed at Baseline, Year 1 and Year 3 (but not Year 2) including NMR Lipoprofile, fasting glucose and insulin, hemoglobin A1C, creatinine, high sensitivity C-Reactive Protein, and possibly carotenoids.

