*Telephone Clinic Visits (Months 18 and 30).* A follow-up telephone assessment will take place at 18 and 30 months post quit-attempt. At this phone contact, the following factors will be assessed: continuous and seven day point-prevalence tobacco abstinence, the nature of the relapse contexts (environmental context, stress occurrence, use of alcohol, social context and so on), use of any cessation aids, new quit attempts, alcohol use in the last 7 days, tobacco withdrawal symptoms (WSWS), the PrimeScreen qualitative dietary survey, and affective status (PANAS) including suicidality. In total, this telephone assessment is estimated to take between 20 and 30 minutes.

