*Brachial artery reactivity testing (BART):* Endothelial function will be assessed using ultrasound measurement of the brachial artery in response to flow mediated vasodilation (FMD). This dynamic measure of arterial function is impacted immediately by cigarette smoking and is extremely sensitive to rapid changes in risk factors for cardiovascular disease. This will be measured at baseline and at the one-year post-quit attempt visit. Impaired endothelial function is associated with cardiovascular risk factors and prevalent as well as incident cardiovascular disease including among smokers.229-233 This association is dose-dependent, both with increasing pack-years of exposure and varying levels of environmental tobacco smoke. It also seems to be potentially reversible as evidenced by the weaker association seen in former smokers.234 Further studies suggest a synergism between smoking and hypercholesterolemia,232 raising the possibility that smoking potentiates endothelial dysfunction by enhancing LDL oxidation.235,236

Brachial artery endothelial function will be measured noninvasively in the morning in the fasting state by a well-validated technique using high-resolution B-mode ultrasound of the brachial artery.235-239 Subjects who regularly use tobacco-containing products must refrain for 12 hours. After a 10-minute rest in a temperature-controlled room (68-70 F), the diameter of the right brachial artery blood flow are measured at baseline and in response to increased blood flow with a high-resolution (7.5 MHz) linear array vascular ultrasound transducer. Increased forearm blood flow, an endothelium-dependent vasodilator, is induced by inflating a pneumatic blood pressure tourniquet placed around the widest part of the forearm to a systolic blood pressure of 250 mm Hg., the release of which after 4.5 minutes leads to hyperemia. The change in brachial artery diameter in response to hyperemia relative to the baseline diameter defines FMD, which is described as a percentage change from baseline. A single-lead electrocardiogram is monitored throughout the study. Coronary and brachial artery flow-mediated vasodilation are correlated strongly (r=0.79, p<0.001).240 Endothelial function of the brachial artery also predicts future adverse cardiovascular events.235,236 In our laboratory, the coefficient of variation for FMD is 2.9% which compares favorably to that reported in the literature.241-243

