The following methods will be used to determine NMR Lipoprofiles. After a 12 hour fast, approximately 2 cc of blood will be collected into a purple top EDTA specimen tube. This sample will be centrifuged immediately at 3000 rpm for 15 minutes. Plasma will be stored at -70C and shipped to LipoScience, Inc.. The technique LipoScience, Inc. uses to acquire and process the NMR data has been described in detail244,245,247 and consists of three steps: 1) acquisition, in duplicate, of the 400 MHz proton NMR spectra from the plasma specimen at 47C, 2) deconvolution of the lipid methyl group signal envelope appearing in the spectra at approximately 0.8 ppm, which yield the derived NMR signal amplitudes broadcasted by 16 modeled lipoprotein subclasses (Figure 4), and 3) conversion of the signal amplitudes into subclass concentrations using experimentally determined factors that relate the signal amplitudes of isolated subfraction standards to their chemically measured cholesterol and triglyceride concentrations. In general, large VLDL particles (V6, V5), IDL, small LDL (L1), and small HDL (H3, H2, H1) are considered atherogenic and associated with Metabolic Syndrome, as is an increased number of LDL particles.244,245,247

Figure 4.Relationship Between Plasma Lipid NMR Signal and Lipoprotein Subclasses

Carotid IMT, brachial artery enthothelial function testing and NMR lipoprofile testing will occur during Baseline of Project 1 (pre-quit). Because of the rapid changes in response expected for brachial artery endothelial function, it will be assessed again at one year post quit attempt. In contrast, carotid IMT will be assessed three years post quit when beneficial effects of cessation and detrimental effects of continued smoking are most likely to be seen. Finally, NMR Lipoprofile will be assessed at baseline, Year 1 and Year 3 post quit.

Other measures correlated with atherosclerotic risk will be assessed including blood pressure, weight, body mass index, heart and respiratory rate, creatinine, high-sensitivity C Reactive Protein, fasting plasma glucose and insulin, and hemoglobin A1C.

Physical Activity and Physical Fitness

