*Protection Against Risk:* With respect to the treadmill stress electrocardiogram tests, participants will participate only if they do not have contraindications and are clinically stable. Participants will be screened prior to the test by trained physiologists for absolute and relative contraindications to stress testing, using physician reviewed protocols. Participants will have documented clearance by physicians for testing prior to the test, and informed consent will be obtained. Twelve-lead ECGs will be reviewed by a physician prior to the test to ensure that the participant does not have ECG or clinical contraindications to the test. Test termination criteria are also standard for stress testing, including the development of chest pain, more than 1 mm. of horizontal or downsloping ST segment depression in standard leads and other usual ECG criteria in addition to clinical criteria including abnormal hemodynamics, serious arrhythmias, abnormal symptoms, significant dyspnea, or abnormal oxygen saturation measurements. Subjects will be given a telephone number to contact the study physician if they experience serious adverse effects. Adverse events (AEs) and serious adverse events (SAEs) will be assessed at each study visit and study staff will verify that all adverse effects are being addressed either by the subject, his/her regular physician, or offer to have the study physician address the concern. In addition, suicidality will be assessed at every visit and follow-up contact. Individuals who report any suicidal ideation will be contacted by a licensed psychologist who will assess the level of risk and provide referrals as needed. Confidentiality of subject data and information will be accomplished by using subject numbers as unique identifiers, allowing us to keep subject data separate from identifying information. No publications or presentations resulting from this research program will contain any identifying information about individual participants.

Potential Benefits of the Proposed Research to the Subjects and Others

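### Table 4 disagrees with the protocol text on the one-year brachial artery test and on suicidality assessment at the 18- and 30-month calls

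*Protocol*

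**What the plan says.** **Status of the table.** The Measurement and Data Collection Plan points the reader to Table 4 for the timing of data collection across Projects 1 and 2.

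**Brachial artery test.** The Table 4 row "Ultrasound Brachial Artery Response Test (UBART" has one mark, with every later cell empty: Orientation is the only marked time. The text says otherwise in three places:
- Annual In-Person Clinic Visits: "Brachial artery endothelial function will be tested at the Baseline and Year 1".
- Brachial artery reactivity testing: "This will be measured at baseline and at the one-year post-quit attempt visit".
- The timing paragraph that closes the section on advanced lipoprotein testing: "it will be assessed again at one year post quit attempt". It gives the reason, namely that this measure is expected to respond quickly.

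**Suicidality.** Table 4 has a separate row, "Suicidality Assessment", marked at Orientation and at the one-, two- and three-year visits, with both phone columns blank. The section on Telephone Clinic Visits (Months 18 and 30) lists "affective status (PANAS) including suicidality" among the items assessed. Protection Against Risk, in section E, states that "suicidality will be assessed at every visit and follow-up contact".

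**The concern.** A protocol should give one answer to what is measured and when. Here the schedule table and the text give different answers for two items, and the protocol does not say which prevails. A schedule table is a natural source for visit checklists and call scripts, so a missing mark can become a missing measurement.

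For the brachial test, the Year 1 scan is the only post-quit measurement that the text plans. If it were skipped, change in flow-mediated dilation could not be computed for anyone, and no later scan is scheduled to make up for it. Brachial endothelial function is named in Aim 1, is one of the three physiologic measures described in detail, and is listed as a post-quit outcome under Secondary analyses.

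For suicidality, the follow-up described under Protection Against Risk (contact by a licensed psychologist) starts from a participant's report of ideation, so it depends on the assessment taking place. The table and the human-subjects section describe different sets of contacts at which it does.

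**Working it through.** No sample size, error rate or power figure enters this point. The check is a comparison of table cells with text.

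**Step 1. Is the table read correctly?** Table 4 has six time columns: Orientation, One Year, 18-month phone, Two Year, 30-month phone, Three Year. The brachial row holds six cells (one mark, five blanks). The suicidality row also holds six (mark, mark, blank, mark, blank, mark). Other rows carry marks where the text leads one to expect them: PANAS and WSWS in all six columns, CIMT at Orientation and Three Year, blood draw at Orientation, One Year and Three Year. The blanks therefore do not look like conversion damage.

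**Step 2. Count the scheduled times within those six columns.**

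| Item | Table 4 | Text | Missing from Table 4 |
| --- | --- | --- | --- |
| Brachial artery test | 1 (Orientation) | 2 (baseline, one year) | 2 − 1 = 1 (one year) |
| Suicidality | 4 (Orientation, Years 1, 2, 3) | 6 (those four plus months 18 and 30) | 6 − 4 = 2 (months 18 and 30) |

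The suicidality count is limited to Table 4's columns. The Measurement and Data Collection Plan also mentions a 42-month telephone contact, for which the table has no column.

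**Step 3. Does another row close the suicidality gap?** The telephone section words suicidality as part of affective status, and PANAS is marked at both calls. But Table 4 gives suicidality its own row and leaves it blank there, so the PANAS marks do not settle the matter.

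**Step 4. Which brachial entry is the outlier?** Three text statements agree and one gives a scientific reason. The visit description lists brachial testing among the second-day procedures and reduces only Year 2 to a single day. At about 2 hours per day, Year 1 takes 2 × 2 = 4 hours, which matches Table 4's own time row. This is supportive but not decisive, because the Year 1 blood tests also fall on the second day.

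**Step 5. What depends on each item?**
- With a baseline brachial scan only, there is no post-quit value, and the secondary analysis of endothelial function has no outcome.
- Hypothesis 1 is stated in terms of CIMT, and the cardiovascular power calculation uses CIMT. CIMT is marked at Orientation and Three Year in Table 4, as the text requires. Neither the hypothesis nor the power figure changes.

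**The case against.** The strongest reply is that these are clerical omissions with an obvious remedy. Much of that stands.

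- **Nothing says that the table governs.** The protocol says the timetable is shown in Table 4, and the same section then states the one-year brachial test outright. Staff who read the text would schedule it. This is correct, and it makes the harm conditional.
- **The table cannot be followed literally anyway.** It marks vital signs at both phone contacts, and its footnote defines these to include carbon monoxide, blood pressure and weight, which staff cannot measure by telephone. This weakens the idea that the table would override the text. It also shows that the table needs checking.
- **Brachial function is a secondary outcome.** This is correct. Its standing rests on Aim 1 and on the description of the three physiologic measures, not on a principal hypothesis.

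A reader might infer that all 900 Year 1 scans, and suicidality assessment at 900 × 2 = 1,800 calls, will be lost. The documents do not support that. Both figures assume that the text is ignored throughout, and the second ignores the protocol's projected 5% annual attrition (900 × 0.95 × 0.95 ≈ 812 by the end). A reader might also infer that a participant protection has been withdrawn. Two separate sections still commit to it, so an omission from the table is the likelier explanation.

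What survives is the contradiction itself. It lies within the protocol, concerns data collection, and would not be resolved by a statistical analysis plan.

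**Conclusion.** The point holds as an internal inconsistency in the assessment schedule. Relative to the text, Table 4 lacks one brachial artery mark (one year) and two suicidality marks (months 18 and 30).

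The consequence is conditional on Table 4 being used as written. In that case there would be no post-quit flow-mediated dilation, the secondary analysis of brachial endothelial function could not be run, and two phone contacts would lack an assessment that the human-subjects section promises. No principal hypothesis, CIMT analysis or power figure is affected, so this should not be read as the loss of a primary outcome.

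For the brachial test, the text is consistent enough to identify the table as the error. For suicidality, the conclusion is only that the table, the telephone-visit section and the human-subjects section must agree. This review does not say which schedule is right.

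The point merits correction despite its modest size, because a missed Year 1 scan could not be recovered and the correction is simple.

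**What to change.** 1. In Table 4, add the One Year mark to the brachial artery row so that it matches Annual In-Person Clinic Visits, Brachial artery reactivity testing and the timing paragraph after the lipoprotein section. Do this before the first Year 1 visits.
2. Reconcile the suicidality row of Table 4 with Telephone Clinic Visits and Protection Against Risk before the 18-month calls begin, and carry the agreed schedule into the call script.

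The cost is a table correction and a consistency check. The visit description already allows a second day of about 2 hours at Year 1, so the brachial correction adds no visit day beyond what is planned. That section gives time only and says nothing about budget.
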